## Supplementary 1: Study protocol

### Introduction

One in six older adults will suffer a stroke in their lifetime, or one stroke every two seconds worldwide. Of relevance to our study, cerebrovascular disease – such as stroke – is the second most common cause of dementia (i.e., vascular dementia), accounting for up to 38% of all dementia cases. Specifically, a stroke doubles one's risk for dementia. Moreover, impairments in several domains of cognition—including memory, attention, and executive function—are common following stroke. Stroke-related cognitive deficits are associated with other negative outcomes including institutionalization, reduced quality of life, and death. Thus, stroke survivors represent a target population in need of intervention strategies to promote cognitive function and prevent dementia. However, the current standard of care in stroke rehabilitation does not adequately address the clinically important cognitive consequences of stroke – especially for those who are in the chronic phase (i.e., > 12 months since an index stroke).

Current evidence from randomized controlled trials (RCTs) suggests that targeted exercise training is an effective strategy to promote both cognitive and functional brain plasticity in older adults. A meta-analysis concluded that aerobic training has robust but selective benefits for cognitive function; the largest benefits occur for executive function. Rodent models have shown that exercise training induces upregulation of neurotrophic factors within the central nervous system that, in turn, contribute to neural health and myelin recovery following pathological insult.

However, there is insufficient quality evidence for targeted exercise training as an effective strategy to promote cognitive function in stroke survivors. Despite the high prevalence of cognitive deficits and the increased risk for dementia in this population, few randomized controlled trials (RCTs) to date have focused on targeted exercise training on cognitive function. A small-scale RCT of individuals with chronic stroke ( $\geq 6$  months post ischemic stroke) showed improved processing speed following 8 weeks of aerobic exercise training but no effects on other aspects of cognition compared to 8 weeks of stretching. A second small-scale RCT found that a 19-week multi-component exercise training program (adapted from the Fitness and Mobility Exercise [FAME] program) improved general cognition and increased cerebral blood flow compared to a strength program of equal length. A pre-post designed study showed that general cognition and executive function were improved following 6 months of combined aerobic and resistance training in individuals who had experienced a stroke at least 10 weeks prior; however, the lack of a control group precludes causal conclusions. In contrast, a recent RCT did not find that 6 months of aerobic exercise significantly improved aspects of memory and executive function relative to low-intensity balance and tone training. In light of the promising evidence from previous pilot studies, from studies of older adults without chronic stroke, and from mechanistic animal studies, further research of exercise training among individuals with chronic stroke in large-scale, well-designed RCTs is needed.

Nevertheless, the physical ability of stroke survivors to participate in targeted exercise training is often limited. In fact, most stroke survivors adopt or return to sedentary lifestyles after rehabilitation. Post-stroke physical deficits (e.g., balance) are associated with reduced activity participation. Additional barriers to physical activity participation include low self-efficacy and social support. Thus, other strategies to promote cognitive function need to be considered for this population.

An alternative or supplemental behavioral approach might be to intervene with cognitive and social enrichment activities to ameliorate cognitive impairment in the chronic stroke phase. The premise of this strategy is that by engaging in activities that stimulate higher-order cognition (e.g., memory and executive function), cognitive performance is improved and future cognitive decline is mitigated. Rodent models suggest that environment enrichment—e.g., housing in larger cages and in larger groups with varied environmental features—has various positive behavioural, neuro-anatomical, and molecular effects, including following stroke. Few previous studies have tested this proposition among humans with chronic stroke. One 6-month pre-post study showed that a program that combined exercise training using the FAME program (2 days/week) with cognitive and social enrichment (1 day/week) was associated with benefits in aspects of memory and executive functions among individuals who had sustained a stroke at least 12 months prior. Another pilot RCT compared this same multi-component intervention to a wait-list control and found benefits to aspects of executive functions, working memory, and physical functioning. Whether these effects could be attributed primarily to the exercise training or to the social and cognitive activities could not be determined by this study design.

Thus, to better understand the relative effects of exercise training and of cognitive and social enrichment on cognitive function, we aim to conduct a 3-arm, parallel group proof-of-concept RCT comparing the following: 1) exercise training; 2) cognitive and social enrichment activities; and 3) an active control group consisting of stretching and toning activities. Each intervention arm will be 6 months in length and will be followed by a 6-month follow-up period. The results of this proof-of-concept RCT will be used to inform the design of a larger definitive trial. Specifically, it will confirm the feasibility of the study methods and procedures.

## **Methods and analysis**

### **Design Outline**

We will conduct a six-month proof-of-concept RCT and follow-up our study cohort for an additional six months (see Figure 1). There will be a dedicated research coordinator (unblinded) and trained assessor (blinded). Standardized protocols will be developed and study personnel will be trained by the research team. Assessments and intervention classes will occur at a research laboratory on the Vancouver General Hospital campus, Vancouver, Canada.

### **Recruitment**

Recruitment advertisements will be placed in local community centers, stroke support groups, and newspapers in Greater Vancouver. Interested individuals will initially be screened by telephone by the research coordinator using both the inclusion criteria and the modified Physical Activity Readiness Questionnaire (PAR-Q), a screening measure of physical readiness for exercise that requires clearance by a physician to engage in exercise. Those who appear eligible will be invited to an information session. During the information sessions, potential participants will be provided with details of the study and will have the opportunity to ask questions. A consent and screening session will be arranged for those who are interested in participating at the end of the information sessions. Those who remain eligible after the screening session will proceed to baseline assessments after their physician provides: 1) a written recommendation indicating their appropriateness to participate in an exercise program; and 2) a detailed description of their stroke (i.e., when it occurred, lesion location, and lesion type as defined by previous MRI or computed tomography scans).

### ***Inclusion Criteria***

Community-dwelling adults will be included who have had an ischemic or hemorrhagic stroke (confirmed by previous MRI or computed tomography scan). In addition, individuals must meet the following inclusion criteria: 1) are aged 55 years and over; 2) have a history of at least one single stroke of at least one year prior to study enrolment; 3) have a Mini-Mental State Examination (MMSE)  score of  $\geq 20/30$  at screening, including a perfect score on the 3-step command to ensure intact comprehension and ability to follow instructions; 4) are community-dwelling; 5) live in Greater Vancouver area; 6) able to comply with scheduled visits, treatment plan, and other trial procedures; 7) read, write, and speak English with acceptable visual and auditory acuity; 8) not expected to start or are stable on a fixed dose of cognitive medications (e.g., donepezil, galantamine, etc.) during the 12-month study period; 9) able to walk for a minimum of six metres with rest intervals with or without assistive devices; 10) based on interview, have an activity tolerance of 60 minutes with rest intervals; 11) not currently participating in any regular therapy or progressive exercise; and 12) provide a personally signed and dated informed consent document indicating that the individual (or a legally acceptable representative) has been informed of all pertinent aspects of the trial. In addition, an assent form will be provided at baseline and again at regular intervals.

### ***Exclusion Criteria***

Individuals will be excluded who are: 1) diagnosed with dementia of any type; 2) diagnosed with another type of neurodegenerative or neurological condition (e.g., Parkinson's disease) that affects cognitive function and mobility; 2) at high risk for cardiac complications during exercise or unable to self-regulate activity or to understand recommended activity level (i.e., Class C of the American Heart Risk Stratification Criteria); 3) have clinically important peripheral neuropathy or severe musculoskeletal or joint disease that impairs mobility, as determined by his/her family physician; 4) taking medications that may negatively affect cognitive function, such as anticholinergics, including agents with pronounced anticholinergic properties (e.g., amitriptyline), major tranquilizers (i.e., typical and atypical antipsychotics), and anticonvulsants (e.g., gabapentin, valproic acid, etc.); or 5) aphasia as judged by an inability to communicate by phone.

### ***Measurement***

There will be three primary measurement sessions: baseline, 6 months, and 12 months. Baseline measurements will be obtained prior to randomization. Additional secondary measures will be assessed monthly by unblinded assessors throughout the 12-month study. Data will be entered and scored using standard scoring procedures for each measure. Paper files will be held in secure filing cabinets and digital data will be stored on encrypted hard drives in laboratory areas with limited, key card access. All participant materials will be identified by identification number to maintain participant confidentiality.

### ***Screening and Consent Session***

For the screening and consent session, the study coordinator will re-administer the Physical Activity Readiness Questionnaire (PAR-Q) , a screening measure of physical readiness for exercise. Global cognitive function will be assessed using the MMSE  and the

MoCA. Eligible participants will be provided a form to be completed by their family physician to confirm the inclusion/exclusion criteria.

### ***Descriptors and Relevant Covariates***

At baseline, general health, demographics, socioeconomic status, and education will be ascertained by a questionnaire. We will also document each participant's American Stroke Classification, medication history, and type (e.g., ischemic, haemorrhage), location (e.g., middle cerebral artery), and structure (e.g., posterior parietal cortex) of stroke from medical records/family physician. At each of the three primary measurement sessions, we will measure age in years, standing height in centimetres, and mass in kilograms. We will assess ADL using the self-report Functional Independence Measure. Participants will complete the Functional Comorbidity Index to estimate the degree of comorbidity associated with physical functioning.

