### **Sample Size Calculation**

We have designed our trial to allow the evaluation of statistical significance of the treatment effect between groups on the ADAS-Cog-Plus. A number of pharmaceutical RCTs in vascular dementia – a population highly relevant to our proposed study – have shown positive cognitive effects as measured by the ADAS-Cog, and it has been suggested that the ADAS-Cog-Plus shows greater sensitivity to underlying changes in cognition. A previous RCT of physical activity in older adults at risk for Alzheimer's disease with ADAS-Cog as the primary outcome measure demonstrated a standardized effect size of 0.60^17. We used interim results from our PROMOTE study – an exercise RCT in adults with mild sub-cortical ischaemic vascular cognitive impairment – for our sample size estimation. Based on data collected from 15 participants who have completed the RCT, we found the mean change in the ADAS-Cog score was 2.7 (SD=2.3) and 0.87 (SD=3.4) for the exercise training group and the control group, respectively. The minimally clinically relevant change (MCRC) on the ADAS-Cog varies between 3 and 5 points, with a change of  $\geq 4$  being recommended by the Food and Drug Administration. Recently, Schrag and colleagues established the MCRC empirically using data collected from the Alzheimer's disease Neuroimaging Initiative. They found that a 3-point change on the ADAS-Cog is an appropriate MCRC. Assuming a mean change of 3 points on the ADAS-Cog for both the EX and Cog-Plus groups and a mean change of 1 point for the CON group at 6 months, a common standard deviation of 2.85, and an alpha of 0.05, 39

participants per group (i.e., total sample of 117) will provide a power greater than 0.80^79. We then assumed a standardized effect size of 0.7 for the ADAS-Cog-Plus, as it has greater sensitivity to changes in cognitive function compared with the 11- or 13-item ADAS-Cog. After accounting for 15% attrition and 2:2:3 allocation, 34 participants were randomized to the EX group, 34 to the ENRICH group, and 52 to the BAT group, for a total sample of 120.

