## **Statistical Analyses**

### ***Primary Outcome***

This analysis will follow the intention-to-treat principal, such that all randomized participants will be included to estimate treatment effects, irrespective of deviations from treatment protocol (e.g., loss to follow-up, non-compliance). This will be done using linear mixed models using maximum likelihood estimation. The model will include random intercepts and slopes, and fixed effects of time (baseline, month 6, month 12), treatment assignment (CON, EX, Cog-Plus), and their interaction. Baseline MMSE and ADAS-Cog-Plus scores will also be included as fixed effect covariates. Time will be specified as a categorical variable, thus allowing us to examine treatment differences at the primary endpoint (month 6) and then, as a secondary objective, whether those differences persist at the 6-month follow-up (month 12). Two planned simple contrasts will be performed using the Dunnett test. These contrasts will be employed to assess differences between: 1) the EX group and the CON group; and 2) the Cog-Plus group and the CON group. The overall alpha will be set at 0.05. A secondary complete-case analysis will be conducted using this linear mixed model, in which participants with valid data at all time points will be included. As an exploratory strategy, multiple imputation will be used to judge the impact of missingness on the conclusions drawn from this study.

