### ***Secondary & Tertiary Outcomes***

Analyses will be descriptive; no alpha has been allocated. Point and interval estimates for the effect of the intervention on each of the secondary outcomes at six and 12 months will be determined separately using linear mixed models. Multiple linear regression analyses will also be performed to explore the association between change in cognitive function, after accounting for experimental group, baseline age, baseline global cognition, and: 1) superior treatment adherence; 2) change in physical activity levels outside the research protocol; and 3) change in general balance and mobility. Randomization integrity will be determined by examining bias in the blocking sequence used to produce allocation sequence.

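### The exploratory regression of cognitive change adjusts for baseline age, but the primary model does not; prespecifying age there is nearly free and may bring a small gain in precision.

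*Protocol*

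**What the plan says.** Under Descriptors and Relevant Covariates, the Protocol lists background data taken at baseline: "general health, demographics, socioeconomic status, and education will be ascertained by a questionnaire". Age is recorded at every main visit: "At each of the three primary measurement sessions, we will measure age in years". The Measurement section fixes the timing: "Baseline measurements will be obtained prior to randomization".

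Under Statistical Analyses, Primary Outcome, the mixed model has time, treatment and their interaction, and then: "Baseline MMSE and ADAS-Cog-Plus scores will also be included as fixed effect covariates". Age and education are not named.

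Under Secondary & Tertiary Outcomes, a regression relates change in cognitive function to adherence, outside physical activity and mobility, "after accounting for experimental group, baseline age, baseline global cognition". Education is not in that list. Of this family of analyses the Protocol says: "Analyses will be descriptive; no alpha has been allocated".

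Two design features bear on the point. The Inclusion Criteria set a minimum age of 55, and no maximum appears there or in the Exclusion Criteria. Under Treatment Allocation and Concealment the only stratification factor is one prior stroke against two or more.

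**The concern.** In one model of cognitive change the authors keep age alongside baseline cognition. Age can confound an association with cognitive change there only if it is related to that change once baseline cognition is held fixed. If it is, adding age to the primary model would also remove some residual variance. The confirmatory model leaves age out, and the text does not say why.

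What is at stake is precision, and protection against a chance imbalance in the one trial that is run. The age range is open at the top, the design does not balance age, and the two active arms have 34 participants each. A covariate fixed in advance also avoids an argument over post hoc adjustment if the arms happen to differ in age.

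**Working it through.** **Inputs from the Protocol.** Difference 3 − 1 = 2 points; "a common standard deviation of 2.85, and an alpha of 0.05"; 39 per group for power above 0.80; standardised effect 0.7 for ADAS-Cog-Plus; 34, 34 and 52 randomised; 15% attrition. On multiplicity: "Two planned simple contrasts will be performed using the Dunnett test".

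**Assumed.** Two-sided tests, a month-6 comparison treated as an analysis of covariance, 0.7 taken in units of the residual SD of the planned model, and the partial R-squared of the added covariates given baseline ADAS-Cog-Plus and MMSE. The Protocol gives no value for this last input, so a range from 0 to 0.10 is shown.

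**1. The plan's own figure.** By the normal approximation, n = 2 × (z₁ + z₂)² × (2.85/2)².
- Alpha 0.025 per contrast: 2 × (2.241 + 0.842)² × 2.031 = 38.6, so 39 per group, with power 0.804.
- Alpha 0.05: n = 32, and power at 39 is 0.873.

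The stated 39 is reproduced.

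**2. Standard error and power, age and education together.** SE ratio = √(1 − R²). Power per contrast uses the non-central t at 0.7/√(1 − R²), two further degrees of freedom spent, and simulated Dunnett critical values of 2.251 (34 v 52) and 2.255 (29 v 44). After attrition, 34 × 0.85 = 28.9 and 52 × 0.85 = 44.2.

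| Assumed partial R² | SE ratio | Power, 34 v 52 | Power, 29 v 44 |
|---|---|---|---|
| 0 | 1.000 | 0.821 | 0.748 |
| 0.02 | 0.990 | 0.829 | 0.757 |
| 0.05 | 0.975 | 0.841 | 0.771 |
| 0.10 | 0.949 | 0.862 | 0.795 |

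**3. Cost of the extra coefficients.** With df = N − 3, estimating k more coefficients multiplies the variance by about (df − 4)/(df − 4 − k).
- Two coefficients, N = 120 (df = 117): 113/111, break-even R² = 1 − 111/113 = 0.018. After attrition (29 + 29 + 44 = 102, df = 99): 95/93, break-even 0.021.
- Age alone, N = 120: 113/112 = 1.009, break-even 0.009. After attrition: 95/94 = 1.011, break-even 0.011.

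The power columns above do not include this factor. With it, the two-covariate SE ratio at R² = 0.05 and 34 v 52 is √(0.95 × 113/111) = 0.983. That is close to the uncorrected ratio at R² = 0.03 (0.985, power 0.833), so the net gain is nearer 1 point than 2.

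**4. What partial R-squared is plausible for one covariate.** Let it correlate rx with the baseline score and ry with the month-6 score, and let those two scores correlate rb. Then partial r = (ry − rx·rb)/√[(1 − rx²)(1 − rb²)]. All correlations are assumed.
- rx = ry = 0.3, rb = 0.8: 0.06/√(0.91 × 0.36) = 0.105, R² = 0.011.
- rx = ry = 0.5, rb = 0.7: 0.15/√(0.75 × 0.51) = 0.243, R² = 0.059.
- Acting only through the baseline score (ry = rx·rb): R² = 0.

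**5. Chance imbalance.** The SD of a standardised baseline difference at 34 v 52 is √(1/34 + 1/52) = 0.22. A difference above 0.25 SD has about a 26% chance per contrast. At the two-sided 5% point (1.96 × 0.22 = 0.43 SD) and an assumed partial R² of 0.05, the contrast shifts by 0.43 × √0.05 ≈ 0.10 residual SD, against a design effect of 0.7.

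**The case against.** The case against making anything of this is strong, and most of it stands.

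- **The Protocol does not contradict itself.** A reader might infer from the section heading that every listed item was meant for the primary model. The heading covers descriptors as well as covariates, the list also holds height, mass, medication and comorbidity, and nothing promises adjustment.
- **The regression asks another question.** Adherence, activity and mobility change are not randomised, so controlling for age is a natural precaution. It shows that the authors thought age might matter beyond baseline cognition. It does not show that age does matter, or that a randomised contrast needs it.
- **The main adjustment is already made.** A reader might infer that an age imbalance passes straight into the month-6 contrasts. It does not: whatever acts through baseline cognition is adjusted for. The remainder averages to zero over randomisations and is covered by the confidence interval.
- **The gain may be nil.** Zero is a possible partial R-squared, and small values do not repay the coefficients.
- **Education is weakly supported.** It is absent from the exploratory regression, and the Protocol gives no unit for it.

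What remains is narrow. The Protocol itself names the covariates of its confirmatory model, has a pre-randomisation variable that it uses in a related model, and does not explain the difference.

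**Conclusion.** The point holds as a minor improvement to the primary model, for age only. The planned analysis is valid and its contrasts are not biased by the omission. The stronger reading, that the plan definitely gives away precision by leaving out age and education, is not supported: the Protocol reports no correlation of either with the outcome. Over an assumed partial R-squared of 0 to 0.05 for the two together, the effect runs from a slight loss to a net fall in standard error of about 1.5%. Only near 0.10 does the power gain reach about 4 to 5 points before the cost of the coefficients. For age alone the break-even is about 0.01. These sizes rest on the assumed range, on treating month 6 as an analysis of covariance, and on reading the effect of 0.7 in residual SD units.

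**What to change.** In Statistical Analyses, Primary Outcome, add baseline age in years to the fixed-effect covariates before unblinding. Name the baseline value, because age is recorded again at months 6 and 12. If the authors prefer to leave age out, one sentence should say why it belongs in the exploratory regression and not here.

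The change is one sentence and needs no new data. The cost is one degree of freedom: if age adds nothing, the variance of the contrasts rises by about 1% (113/112 at full enrolment, 95/94 after attrition). Education may be considered in whatever form it is recorded; if that is categorical it costs more than one degree of freedom. Covariates for the secondary-outcome models can be left to the SAP.
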